**Methods:**

The sample comprises 70 participants aged 60–75 years, who have GAD. Exclusion criteria comprise substance abuse and unstable medication; inability to participate in physical exercise; and conditions which precludes GAD as primary diagnosis. The interventions are individual treatment in the outpatient clinic at the local psychiatric hospital, with two experimental arms: (1) CBT + physical exercise and (2) CBT + telephone calls. The primary outcome measure is symptom reduction on the Penn State Worry Questionnaire. Other measures include questionnaires, clinical interviews, physiological, biological and neuropsychological tests. A subset of 40 participants will undergo magnetic resonance imaging (MRI). After inclusion, participants undergo baseline testing, and are subsequently randomized to a treatment condition. Participants attend five sessions of the add-on treatment in the pre-treatment phase, and move on to interim testing. After interim testing, participants attend 10 sessions of CBT in parallel with continued add-on treatment. Participants are tested post-intervention within 2 weeks of completing treatment, with follow-up testing 6 and 12 months later.

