## Method

### Study design

The study is a 2 × 2 mixed factorial design (Time x Group) with participants randomized to one of two treatment conditions: (1) CBT combined with physical exercise (CBT + PE) or (2) CBT combined with telephone call attention placebo (CBT + AP). Participants complete pre-treatment, interim and post-treatment outcome measures, in addition to follow-up tests at 6 and 12 months after treatment.

Participants in both treatment conditions attend a 5-week pre-treatment period. The pre-treatment period has a two-part rationale. The first 5 weeks of physical exercise are aimed at introducing the participant to the exercises with a focus on adjustment and neuromuscular facilitation [64]. In addition, resting BDNF has been shown to increase after 5 weeks of physical exercise [65]. The primary goal of the pre-treatment period is to ensure good implementation of physical exercise, and to obtain elevated resting BDNF in the CBT + PE group before the onset of CBT. As such, the pre-treatment period is a measure to facilitate the add-on effects of physical exercise.

Participants receiving CBT + PE attend one supervised and two unsupervised sessions of PE during each of the 5 weeks of the pre-treatment period. Participants receiving CBT + AP receive one telephone call per week during the pre-treatment period.

After the pre-treatment period, the participants receive 10 weekly sessions of CBT combined with either continued physical exercise in the participants receiving CBT + PE or weekly telephone contact in parallel to the CBT sessions in the participants receiving CBT + AP. See Fig. 1 for a display of the study design. The present protocol has been prepared in accordance with relevant items from the Standard Protocol Items: Recommentations for Interventional Trials (SPIRIT) Checklist (see Additional file 1). See Fig. 2 for the SPIRIT figure displaying the schedule of enrolment, interventions and assessments.

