### Participants

Adults, aged 60–75 years (*n* = 70), who have a primary diagnosis of GAD as evaluated by the ADIS-IV [63] will be included. Exclusion criteria are (1) substance abuse; (2) use of benzodiazepines and antipsychotic medication; (3) changes in the dose of other psychotropic medication during the study; (4) medical conditions that preclude participation in physical exercise; (5) severe major depression as determined by the Mini International Neuropsychiatric Interview (M.I.N.I.) [66, 67]; (6) life-time history of psychosis and/or mania; (7) participation in other ongoing psychotherapy; (8) organic brain disease; (9) a score of 25 or less on the Mini Mental State Examination (MMS-E) [68] and (10) participation in physical exercise exceeding 75% of the exercise dose given in the study.

A subsample of 40 participants, who do not the meet exclusion criteria for magnetic resonance imaging (MRI), will be included in a nested MRI study. The exclusion criteria for MRI are (1) MRI-incompatible metal screws or implants; (2) large tattoos on head, neck or upper body; (3) pacemaker and (4) claustrophobic fear, to a degree whereby participants refuse to undergo MRI without sedatives. These exclusion criteria are applied to ensure patient safety.

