#### Physiological and biological measures

Serum BDNF is measured in blood samples and assayed using the Human proBDNF and mBDNF DuoSets [83, 84]. We use an ambulatory electrocardiogram (ECG) [85] to measure HRV. Physical fitness is measured by the Ekblom-Bak submaximal cycle ergometer test [86], the Five-Minute Pyramid Test [87] is used for prediction of maximal oxygen uptake (VO_2_ max) and items from the Senior Fitness Test are used for measuring submaximal physical strength [88].

The study will investigate potential mediators and moderators of treatment outcome. Cortisol is measured in three saliva samples collected during the assessment days, and is analysed using the cortisol saliva luminescence immunoassay [89]. Genetic material is obtained by one saliva sample at baseline, and analysed using the TaqMan method [90]. Participants wear the Philips Actiwatch 2 [91] for 1 week at baseline, post-intervention and at 12-month follow up to measure activity level and sleep variables.

A subsample of 40 participants undergo MRI at baseline, post testing and at 12-month follow-up testing. MRI will be performed using a GE Signa 3 .0T twin speed HDxt scanner [92]. A head coil with video goggles allows for the Eriksen flanker task [93] to be applied during functional MRI.

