### Power analysis and statistical analysis

Power estimates were calculated using the G* Power 3 programme [103]. Treatment effects will be investigated by an intention-to-treat approach to data analysis using a hierarchical linear model, whereby therapists will be included at the second level to account for potential nesting by this factor. Power analysis for effects are estimated with conservative repeated measures analysis of variance (ANOVA) (within-between interactions). For the primary outcome measure, based on previous studies [22, 28], the difference in effect size is set to *d* = 0.35, alpha = 0.05, correlation between repeated measures 0.5, two measurements (pre/post), a total of 70 subjects (*n* = 35 in each group) yielding power above 0.82. Moderators and mediators will be investigated using linear multiple regression, fixed model, single coefficients. An effect size set to *f*^*2*^ = 0.15, two-tailed tests, alpha = 0.05 and *N* = 70 yields power above 0.95 with four predictors. For the subset of functional MRI (fMRI) assessments the following statistics and power analysis will be applied: task-fMRI data will be analysed using General Linear Model in SPM12 for pre-processing and single subject and group analyses, GIFT [104] to investigate the functional and structural data, and arterial spin labelling (ASL) data will be analysed in SPM12. Region of interest (ROI) will be analysed for both structural and functional data (SPM12) to extract blood oxygen level dependent (BOLD) responses to test correlation with specified variables. Expecting percent signal changes of approximately 0.5% at the single voxel and spatial smoothing at full width at half maximum (FWHM) of 5 mm (provides an estimated effect size of *d* = 0,7), using the two-tailed independent samples *t* test, an allocation rate of 1, alpha set to 0.05, correlation between repeated measures 0.5 and a total sample size of 80 (40 in each group) yields power above 0.87. For differences between pre-treatment and post treatment data using the same parameters, the matched-pairs *t* test with 20 subjects yields power above 0.90. Treatment effects are estimated using conservative repeated measures ANOVA (within-between interaction), and conservatively setting the estimated value of *d* = 0.35, alpha set to 0.05, two measurements (pre, post), correlation between repeated measures 0.5, and 60 subjects (*n* = 20 per group) yields power above 0.83. Based on these calculations, the estimated power values indicate that risk of committing type II errors is adequately controlled.

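### MRI power is stated for 80 and 60 subjects, but the nested MRI study has 40 in two arms; at 20 per arm the stated 0.87 and 0.83 are both about 0.58

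*Protocol article*

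**What the plan says.** The size of the MRI study is given three times in the Protocol article, each time as 40 in total:

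- Abstract, Methods: "A subset of 40 participants will undergo magnetic resonance imaging (MRI".
- Participants: "A subsample of 40 participants, who do not the meet exclusion criteria for magnetic resonance imaging (MRI), will be included in a nested MRI study".
- Physiological and biological measures: "A subsample of 40 participants undergo MRI at baseline, post testing and at 12-month follow-up testing".

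The Abstract gives the whole trial as 70: "The sample comprises 70 participants aged 60–75 years, who have GAD". Study design gives two arms: "participants randomized to one of two treatment conditions".

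The section Power analysis and statistical analysis then gives three power figures for the fMRI subset:

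1. Independent-samples t test, two-tailed, d = 0.7, alpha 0.05, equal allocation: "a total sample size of 80 (40 in each group) yields power above 0.87".
2. Matched-pairs t test for pre- to post-treatment change, said to use the same parameters: "test with 20 subjects yields power above 0.90".
3. Repeated-measures ANOVA interaction, d = 0.35, two measurements, correlation 0.5, 60 subjects, with n given as "20 per group) yields power above 0.83".

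The section closes by concluding that the risk of type II error is adequately controlled.

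**The concern.** The three sample sizes do not describe one MRI study. Eighty is twice the MRI subset and ten more than the trial enrols. Sixty at 20 per group makes three groups, and only two arms are described. Only the 20 in the matched-pairs calculation fits, as one arm of a 40-person subset.

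The article draws a conclusion from these figures. If the between-arm MRI comparisons have much less power than stated, a reader who relies on that conclusion would give a null imaging result more weight than it can bear.

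**Working it through.** **Inputs.** MRI subset 40 (Abstract, Participants, Physiological and biological measures); two arms (Study design); d = 0.7, d = 0.35, alpha 0.05, correlation 0.5 and two measurements (Power analysis and statistical analysis). Assumed, because the article does not state it: the MRI comparison is between the two arms, with 20 participants in each.

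**Formulas.**
- Independent t test: noncentrality d·√(n/2), df = 2n − 2, n per group.
- Matched pairs: dz = d/√(2(1 − ρ)) = 0.7/√1 = 0.7; noncentrality dz·√n, df = n − 1.
- Interaction, in the G*Power form: λ = f²·N·m/(1 − ρ), df1 = (k − 1)(m − 1), df2 = (N − k)(m − 1), with f = d/2 = 0.175, m = 2, ρ = 0.5.

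**Calibration.** For the primary outcome (N = 70, k = 2), λ = 0.030625 × 70 × 2/0.5 = 8.575, df 1 and 68, power 0.823. The article states above 0.82, so this convention is the one the article used.

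**1. Between-group t test, d = 0.7, two-tailed.**

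| n per group | noncentrality | df | power |
|---|---|---|---|
| 40 (as stated) | 3.130 | 78 | 0.871 |
| 20 (MRI subset of 40) | 2.214 | 38 | 0.578 |

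The stated 0.87 reproduces, but only at 40 per group. With 20 per group, power reaches 0.80 at d of about 0.91. Unequal splits lower it slightly: 0.574 at 18/22, 0.561 at 16/24, 0.539 at 14/26. Even scanning all 70 participants (35 per arm) would give 0.823.

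**2. Interaction, f = 0.175, two measurements.**

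| N | groups | λ | df | power |
|---|---|---|---|---|
| 60 | 3 | 7.35 | 2, 57 | 0.654 |
| 60 | 2 | 7.35 | 1, 58 | 0.760 |
| 40 | 2 | 4.90 | 1, 38 | 0.578 |

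The stated 0.83 is not reached with 60 subjects under either group count. The nearest variant tried, two groups with three measurements, gives 0.844, but the text specifies two measurements. At N = 40, varying the correlation from 0.3 to 0.7 moves power from 0.45 to 0.80, so 0.83 is not reached there either.

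**3. Matched pairs, n = 20, dz = 0.7.** Noncentrality 0.7 × √20 = 3.130, df = 19. Two-tailed power is 0.844; one-tailed it is 0.915. Two-tailed power of 0.90 needs 24 pairs.

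**The case against.** The strongest reply is that the article never says the 80-subject test compares the two treatment arms. Forty per group equals the full MRI subset, and 60 at 20 per group is three groups, so a comparison with people outside the trial would fit the counts. That stands as a caution: the contradiction in counts is certain, while the 0.58 depends on reading the test as between arms. It does not rescue the figures, because no outside group is described, and the 0.83 fails with three groups as well. The 20/20 split is also inferred, from equal allocation and the 20 per group in the text, but less balanced splits only reduce power.

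Three stronger readings are tempting and are not supported:

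- A reader might blame the 80 and 60 for the 0.90 as well. That calculation uses 20 subjects, which is consistent with the subset. Its fault is sidedness, and pooling all 40 would give a two-tailed power of 0.99.
- A reader might put the interaction power at 0.19, taking d = 0.35 as the between-arm difference in change. That changes the meaning of the effect size rather than correcting the MRI count, and it departs from the convention that reproduces the primary-outcome figure.
- A reader might treat the whole drop from 0.83 to 0.58 as a sample-size effect. Part of it is that 0.83 does not follow from its own inputs.

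It can also be said that MRI is a nested study and that the primary outcome is worry score in 70 participants. That is right, and it limits how far the point reaches.

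**Conclusion.** The point holds for the MRI power statement. The 80 and 60 cannot be reconciled with a 40-person subset in two arms. Assuming a between-arm comparison with 20 per arm, power is about 0.58 at d = 0.7 and about 0.58 for the interaction at f = 0.175 with correlation 0.5. That is a type II risk of about 42% (1 − 0.58) at the article's own assumed effects. The 0.90 for 20 pairs is a separate and smaller error: it should read 0.84 if the test is two-tailed, as the stated parameters imply.

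The closing statement on type II error is therefore unsupported for between-arm MRI comparisons. Nothing here affects the primary-outcome power figure, which reproduces at 0.823.

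**What to change.** In Power analysis and statistical analysis:

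- Reconcile the 80 and 60 with the planned 40, and name the groups each MRI test compares. If a comparison group outside the trial was intended, describe it.
- Restate MRI power for 40 participants in two arms: about 0.58 between arms at d = 0.7, and about 0.58 for the interaction at f = 0.175. State the split by arm that is assumed.
- Give the detectable effect at 20 per arm: d of about 0.91 for 80% power.
- State the sidedness of the matched-pairs test, and give 0.84 for 20 pairs if two-tailed.
- Withdraw or qualify, for between-arm MRI comparisons, the sentence that type II error is adequately controlled.

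This costs wording only, with no change to design, recruitment or the primary analysis. The stated MRI power becomes less favourable.

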#### Neuropsychological testing

IQ level will be assessed with two subtests, Vocabulary and Matrix Reasoning, from the Wechsler Abbreviated Scale of Intelligence [77]. Psychomotor speed and hand-eye coordination will be measured using the Grooved Pegboard Test [78], and the subtest, Coding, from the Wechsler Adult Intelligence Scale – Fourth Edition [79]. Executive functions will be assessed using the Wisconsin Card Sorting Test: Computer Version 4 research edition [80], alongside three subtests from Delis-Kaplan Executive Function System battery [81]: Trail Making Test, the Verbal Fluency Test, and the Color-Word Interference Test, and working memory is assessed using the subtest, Numbers, from the WAIS-IV [79]. Verbal memory will be measured using the California Verbal Learning Test [82].

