
To control for type 1 errors, the secondary clinical outcome inventories will be assessed in two stages, initially together, and if significant they will be analysed separately. Pre-treatment differences on continuous and categorical demographic variables between the two treatments will be assessed using the independent samples *t* test and Fisher’s exact test, respectively. Other changes and differences in continuous variables will be assessed using the repeated and independent samples *t* test, and Fisher’s exact test and McNemar’s test to determine proportional differences between or within groups, respectively. Repeated testing within the same domain will be controlled for multiple testing using the Holm-Bonferroni method [105].

Missing data will be handled within the hierarchical linear model analyses. For analyses where this is not appropriate, last observation carried forward (LOCF) will be applied. For inventories, missing data will be replaced by the mean, provided that no more than 20% of values/item for this measure are missing. If more than 20% of values/item are missing, data will be considered invalid, and will be handled as missing as described. The potential impact of compliance with the different treatment elements will be addressed in separate analyses.

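### The stated power above 0.95 for a moderator or mediator coefficient is about 0.89 on its own inputs, and lower still if the Holm-Bonferroni rule covers these regressions

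*Protocol article*

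**What the plan says.** The Protocol article, section Power analysis and statistical analysis, gives the model: "Moderators and mediators will be investigated using linear multiple regression, fixed model, single coefficients". The inputs are "An effect size set to *f*^*2*^ = 0.15" and "two-tailed tests, alpha = 0.05 and *N* = 70", and the result is that this "yields power above 0.95 with four predictors". The paragraph ends by concluding that, on these calculations, the type II error risk is under adequate control.

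The next paragraph of the section deals with type I error. The secondary clinical inventories are tested first together and then separately. Baseline differences and other changes are tested with t tests, Fisher's exact test and McNemar's test. The paragraph on testing then closes with "Repeated testing within the same domain will be controlled for multiple testing using the Holm-Bonferroni method". It does not define a domain, give a number of tests, or mention the moderator and mediator regressions.

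Several mechanism constructs are measured more than once. Under Neuropsychological testing, "Executive functions will be assessed using the Wisconsin Card Sorting Test: Computer Version 4 research edition", together with three D-KEFS subtests, and the same sentence adds Numbers for working memory. Under Physiological and biological measures, BDNF is assayed as proBDNF and mBDNF. That section also says: "The study will investigate potential mediators and moderators of treatment outcome".

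**The concern.** The power figure is computed for one coefficient at an unadjusted 0.05, while the plan also carries a multiplicity rule that could apply when several measures of one construct are tested. If it does apply, the first rejection in a domain of k tests needs a p-value of at most 0.05/k, and the power statement makes no allowance for that. The figure also has to be right at 0.05 before any adjustment, and it is not.

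What is at stake is how a null mechanism result would be read. The trial's hypotheses give BDNF, heart rate variability and cognition a central role, and the Discussion presents the study of mediators as a strength. A reader who trusts power above 0.95 would take a non-significant coefficient as good evidence against a medium-sized effect, with a miss rate below 1 in 20. On the stated inputs the miss rate is about 1 in 9 for one unadjusted test (1 − 0.891 = 0.109).

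**Working it through.** **Inputs**, all from Power analysis and statistical analysis: f² = 0.15, N = 70, four predictors, two-tailed alpha 0.05, test of one coefficient. The number of tests per domain, k, is not given and is treated as an assumption below.

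**Step 1: the plan's own figure.** For a single coefficient in a fixed-model regression:

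- noncentrality = √(f² × N) = √(0.15 × 70) = √10.5 = 3.24
- degrees of freedom = 70 − 4 − 1 = 65
- two-tailed critical t at 0.05 = 1.997
- power = P(|T| > 1.997) under the noncentral t = **0.891**

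The stated figure is above 0.95, so it is not reproduced; the gap is about 6 points.

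**Step 2: could another reading give 0.95?**

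| Variant | Power |
|---|---|
| Two-tailed, 1 to 5 predictors | 0.891 to 0.892 |
| Normal approximation, two-tailed | 0.900 |
| 0.15 read as R² (f² = 0.15/0.85 = 0.176) | 0.933 |
| One-tailed | 0.941 |
| Omnibus F test of all four predictors | 0.704 |

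None exceeds 0.95. The one-tailed test comes closest but contradicts the stated sidedness. Two-tailed power of 0.95 would need N = 89, or f² a little above 0.19 at N = 70.

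**Step 3: effect of the Holm-Bonferroni rule, if it covers these regressions.** The range k = 2 to 5 is an assumption. It is suggested by two BDNF assays and four or five executive and working-memory measures, with one score per instrument. The second column applies the Step 1 formula at alpha 0.05/k, Holm's strictest step. The last two columns come from simulating the full step-down procedure with independent tests, each real effect having f² = 0.15. They give the average power per real effect.

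| k | Power at 0.05/k | Full Holm, one real effect | Full Holm, all k real |
|---|---|---|---|
| 2 | 0.825 | 0.83 | 0.88 |
| 3 | 0.781 | 0.78 | 0.87 |
| 4 | 0.747 | 0.75 | 0.86 |
| 5 | 0.720 | 0.72 | 0.84 |

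With one real effect, the multiplicity step costs about 7 points at k = 2 (0.891 − 0.825) and 17 points at k = 5 (0.891 − 0.720). If all effects are real, it costs about 1 to 5 points. Every entry lies below 0.89.

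**The case against.** The strongest reply is that the Holm sentence may not concern these analyses at all. It directly follows the t, Fisher and McNemar tests, whereas the regressions stand in the previous paragraph without any multiplicity statement. No family size is given, and the count of executive measures comes from a list of instruments that does not name them as separate mediators; a composite score is equally possible. Nominal-alpha power for a single secondary coefficient is ordinary practice, and an article may leave the definition of test families to a fuller document.

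All of this stands, and it limits what can be claimed. A reader might infer that the plan's own rule fixes the power at 0.72 to 0.82. The documents do not support that: the rule's reach and k are not stated, and the range is Holm's strictest step with only one real effect. A reader might also infer that 0.95 is correct at an unadjusted 0.05 and merely belongs to a different decision rule, so that multiplicity alone turns a miss rate of 1 in 20 into 1 in 4. That is wrong too, because the unadjusted figure is already 0.89 and about 6 points of the gap have nothing to do with multiplicity.

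The reply does not rescue the printed number. If Holm does not apply, the power is 0.89; if it does, it is lower.

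**Conclusion.** The point holds in a limited form. The firm part is that power above 0.95 does not follow from the stated inputs, which give 0.89; this needs no assumption beyond the standard test of one coefficient that the plan names. The conditional part is that, if the Holm-Bonferroni rule covers the moderator and mediator regressions, power drops further. For an assumed 2 to 5 coefficients per domain it is about 0.83 down to 0.72 with one real effect, and about 0.88 down to 0.84 if all are real. These ranges rest on one score per instrument and f² = 0.15 for each real effect, with the simulated values also assuming independent tests.

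The general conclusion on type II error is therefore too favourable for the mechanism analyses. The primary PSWQ comparison and its sample size have a separate calculation and are not touched by this point.

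**What to change.** In Power analysis and statistical analysis:

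- Replace power above 0.95 with about 0.89 for one two-tailed, unadjusted coefficient.
- For domains in which several measures will be tested under Holm-Bonferroni, give the lower adjusted range and state the number of tests assumed. With 2 to 5 tests this is about 0.83 to 0.72 with one real effect, and about 0.88 to 0.84 if all are real.
- Limit the closing sentence on type II error so that it does not extend a 0.95 assurance to the moderator and mediator analyses, and report null mechanism results with that in mind.

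The cost is a change of wording and a less favourable stated power. No extra patients or data are needed.

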Previous studies investigating long-term physical exercise as an adjunct to with CBT for treatment of anxiety disorders have shown mixed results. One study had null findings [57], two studies indicate benefits of adjunct physical exercise [58, 59] and one feasibility study concluded that add-on physical exercise is feasible and potentially beneficial [60]. The study that did not find positive effects of CBT combined with physical exercise was in a non-clinical sample [57], which suggest a limited added effect of physical exercise in a non-clinical population. A recent study on physical exercise combined with exposure therapy for panic disorder demonstrated the lack of a significant effect of adjunct physical exercise. The authors point to ceiling effects as the reason for the lack of effect of the add-on treatment, as exposure therapy already has high treatment efficacy [61]. This is in line with a point made by other authors, that physical exercise could be a more potent intervention in groups in whom treatment with CBT has limited effects (e.g. [62]).

Based on this rationale, the aim of the present study is to compare the effects of physical-exercise-augmented CBT to standard CBT combined with a placebo control condition. We expect that exercise-augmented CBT will yield better results than standard CBT as measured by our primary outcome measure, symptom reduction on the Penn State Worry Questionnaire (PSWQ) [23]. The proportion of patients who achieve remission as assessed by an independent clinical assessor using the Anxiety Disorders Interview Schedule for DSM-IV (ADIS-IV) [63], will be assessed as a secondary outcome measure. We also expect levels of BDNF at baseline to be positively related to treatment outcome, and that the participants that receive augmented CBT will improve significantly in the cognitive measures and in levels of BDNF following treatment as compared to the CBT alone group. Furthermore, we expect HRV to improve with exercise-augmented CBT, and that these changes will correlate with clinical change, and changes in cognitive functions and BDNF levels.

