In addition to expecting more symptom reduction on the PSWQ in participants receiving CBT + PE, we also expect these participants to gain improved HRV and elevated baseline and acute BDNF levels at the post-treatment and follow-up measurements, as compared participants receiving CBT + AP. We will also explore whether these measures change over treatment in both treatment arms, and if so, how this change evolves over the follow-up measures. Furthermore, we expect CBT + PE to positively affect cognitive functions as measured by our neuropsychological test battery, as compared to CBT + AP. One potential limitation to this approach is the learning effects in repeated neuropsychological testing. We do expect learning effects, especially with the Wisconsin Card Sorting Test, and the California Verbal Learning Test. However, we control for this by repeating the testing in both treatment conditions and by comparing the groups.

The current study has both strengths and limitations that should be noted. One of the strengths of this study is the large number of tests and measures at multiple time points. This allows for investigation of mediators of treatment efficacy, which otherwise would be impossible to measure. However, the number of tests and measures could also pose more strain on participants, which might increase the risk of drop-out at the post-treatment and follow-up test points. We work actively to reduce this risk by coordinating the tests and treatment closely, and calling participants to schedule follow-up tests. By administering many questionnaires, we also have an increased risk of missing data. We monitor this by being physically present or available to participants as they complete the questionnaires, which allows us to reduce the number of missing responses.

With this study, we aim to fill some of the gaps in the existing knowledge on GAD in older adults. The study design allows us to investigate the effect of physical exercise as an augmentation to CBT. We also investigate long-term effects through follow up of the participants; additionally, we include several measures that allow us to examine both treatment effects and possible mediators and moderators of treatment outcome. Some important implications of this study will be to ensure accurate and more available treatment programmes for older adults.

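### LOCF is the stated fallback for outcomes outside the hierarchical model, chiefly remission; if dropout differs by arm it creates a spurious arm difference, though the primary PSWQ analysis is unaffected

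*Protocol article*

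**What the plan says.** All of the following is in the protocol article's section on power and statistical analysis unless another section is named.

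- Main analysis: "Treatment effects will be investigated by an intention-to-treat approach to data analysis using a hierarchical linear model", with therapist at the second level.
- Missing data in that model: "Missing data will be handled within the hierarchical linear model analyses".
- Missing data elsewhere: "For analyses where this is not appropriate, last observation carried forward (LOCF) will be applied". No alternative and no sensitivity analysis is named.
- Tests outside the model: "Other changes and differences in continuous variables will be assessed using the repeated and independent samples *t* test", and for binary outcomes Fisher's exact test and "McNemar’s test to determine proportional differences between or within groups, respectively". Moderators and mediators go to multiple regression.
- The Background names a binary secondary outcome: "The proportion of patients who achieve remission as assessed by an independent clinical assessor".
- The Discussion says that the number of tests and measures could strain participants, "which might increase the risk of drop-out at the post-treatment and follow-up test points". It gives no rate, overall or by arm. On repeated cognitive testing it adds: "We do expect learning effects, especially with the Wisconsin Card Sorting Test, and the California Verbal Learning Test".

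**The concern.** LOCF scores a participant who leaves before post-treatment as unchanged since the last visit, although both arms receive CBT and would be expected to change. One who leaves before follow-up is scored as holding the last value. If one arm loses more participants, it has more of these frozen values, and the arm means separate without any treatment effect.

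The visit schedule decides what is carried. As far as the text shows (the schedule figure was not available to me):

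- The ADIS-IV is described at inclusion and after treatment only. A missing post-treatment interview therefore becomes GAD present, that is, not remitted.
- Interim testing has no neuropsychological tests. Post-treatment cognition would always be carried from baseline, which removes both any benefit and the practice gain that the authors expect.
- BDNF and ECG are repeated at interim. The pre-treatment period is meant to raise resting BDNF in the exercise arm by then, so a carried interim value could favour that arm.

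Unequal loss is plausible. The exercise arm has three sessions of 45–60 minutes a week, and the control arm has one call of at most 20 minutes. At stake is the credibility of the secondary and mechanistic results, remission first.

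**Working it through.** **The plan's own figure.** The plan gives no number that depends on LOCF. Its primary power figure (above 0.82) reproduces. With f = 0.35/2 = 0.175 and λ = N·m·f²/(1−ρ) = 70 × 2 × 0.175²/(1−0.5) = 8.575 on 1 and 68 df, power is 0.823. LOCF plays no part in it.

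**Inputs.** From the protocol: 35 per arm, alpha 0.05, correlation 0.5 between repeated measures. Assumed, because the protocol gives no values: dropout by arm and mean change over time. SD is set to 1.

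**Bias formula.** Let both arms truly change by Δ, with dropout p₁ and p₂ completely at random and baseline carried forward. The mean LOCF change in arm j is (1−pⱼ)Δ, so

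spurious difference = (p₁ − p₂) × Δ.

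For 30% against 10% and Δ = 1 SD this is 0.20 × 1 = 0.20 SD.

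**Null rejection.** Simulation, 10,000 trials per setting, no true arm difference, t test on LOCF change. Monte Carlo standard error near 5% is √(0.05 × 0.95/10,000) ≈ 0.2 percentage points. Cells show rejection at nominal 5%, with bias in brackets.

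| Change in both arms | Dropout 20/10% | 30/10% | 40/10% |
|---|---|---|---|
| 0.5 SD | 5.7% (0.05 SD) | 7.6% (0.10 SD) | 11.0% (0.15 SD) |
| 1.0 SD | 7.0% (0.10 SD) | 14.4% (0.20 SD) | 26.8% (0.30 SD) |
| 1.5 SD | 8.9% (0.15 SD) | 22.1% (0.30 SD) | 42.4% (0.45 SD) |

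Checks:

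- Equal dropout (20/20%, 1 SD): 4.9%. With no change over time it also stays near 5%.
- Complete cases at 1 SD and 30/10%: 5.1%. They are valid here because dropout is completely at random.
- Interim value carried instead of baseline, with no change by interim (1 SD, 30/10%): 12.0%.

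**Either direction.** Take a true benefit of 0.35 SD and a 1 SD change in the control arm (illustrative only). Dropout of 30% in the exercise arm and 10% in the control arm gives 0.7 × 1.35 − 0.9 × 1 = 0.045 SD. The reverse gives 0.9 × 1.35 − 0.7 × 1 = 0.515 SD.

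**Remission.** Assume true remission of 50% in both arms, with missing counted as GAD present. At 30/10% dropout the scored rates are 0.5 × 0.7 = 35% and 0.5 × 0.9 = 45%. By exact enumeration with 35 per arm, Fisher's test rejects in 9.0% of trials, against 2.4% with no dropout. At 20/10% it is 40% against 45%, and 4.0%.

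**Standard error.** At 1 SD and 30/10%, the t-test standard error of the LOCF difference averages 0.232 and the estimate's actual spread is 0.234. The complete-case standard error is 0.269, so LOCF looks about 14% more precise (0.232/0.269 = 0.86). Because the t-test standard error matches the spread of its own estimate, the excess rejections come mainly from bias.

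**The case against.** Several counter-arguments have force.

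- **Primary outcome.** Treatment effects are analysed in the hierarchical model, which handles missing data itself. A reader might infer that LOCF threatens the PSWQ result, or might measure the bias against the planned d = 0.35. Neither is supported: LOCF does not enter that analysis, and d = 0.35 is set for it.
- **Which outcomes are exposed.** A reader might infer that BDNF, HRV and cognition will all be carried forward. The text assigns them neither to the model nor to the t tests, so they are exposed only if analysed outside the model. Remission is the likeliest case, because Fisher's test is the only between-group test of proportions named, but this too is inferred. Baseline comparisons need no carried values, and item gaps of up to 20% are mean-replaced.
- **Size.** A 1 SD change suits a symptom score. Nothing in the protocol supports it for BDNF, HRV or cognition, and the bias shrinks with the change.
- **Unequal dropout.** It is not documented. The Discussion links dropout to the testing load, which is the same in both arms, and participants with incomplete pre-treatment sessions still go on to interim testing. The gap in treatment burden makes unequal loss plausible, no more.
- **Precision.** A reader might blame too-small standard errors for the false positives. The equal-dropout result (4.9%) shows that they are not the driver.
- **Remission.** At post-treatment, LOCF equals counting missing as not remitted, a familiar convention. It can still mislead when dropout is unequal.

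These points narrow the scope and make the size conditional. They leave the bias mechanism intact.

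**Conclusion.** The concern holds in a limited form. LOCF is fixed in current text as the only participant-level rule outside the hierarchical model. It biases an arm comparison whenever dropout is unequal and the outcome moves, even under the most benign dropout mechanism. Remission is the clearest case; t-test comparisons and mediator regressions follow if they are run outside the model.

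The size is conditional on assumed dropout and change. It ranges from negligible (equal dropout, or no change) to roughly a doubling or tripling of the false-positive rate at 30/10% (14.4% for a 1 SD change; 9.0% against 2.4% for remission). The mechanism is certain and the magnitude is not. This should be changed, but it does not put the primary result in doubt.

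**What to change.** Replace the LOCF sentence with a rule that is valid under missing at random:

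- **Continuous secondary outcomes:** use the same likelihood-based mixed model as for the primary outcome, and say which outcomes it covers.
- **Remission:** use a logistic mixed model or multiple imputation by arm. With one post-baseline interview, imputation has the advantage of drawing on the baseline and interim measures and on the session-by-session GAD-7, collected in both arms. Keep the imputation model small, given 35 per arm.
- **Mediator and moderator regressions:** use the same imputed data sets.
- **Sensitivity:** keep LOCF, or counting missing as not remitted, only as a labelled sensitivity analysis, and report dropout by arm and visit beside it.

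The cost is a little more analysis work. No new data and no change to visits are needed.
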